## Abstract

**Background:**

Supervised exercise therapy (SET) is recommended in patients with symptomatic peripheral arterial disease (PAD) as first‐line therapy, although patient adoption remains low. Home‐based exercise therapy (HBET) delivered through smartphones may expand access. The feasibility of such programs, especially in low‐resource settings, remains unknown.

**Methods:**

Smart Step is a pilot randomized trial of smartphone‐enabled HBET vs walking advice in patients with symptomatic PAD in an inner‐city hospital. Participants receive a smartphone app with daily exercise reminders and educational content. A trained coach performs weekly phone‐based coaching sessions. All participants receive a Fitbit Charge HR 2 to measure physical activity. The primary outcome changes in 6‐minute walking test (6MWT) distance at 12 weeks over baseline. Secondary outcomes are the degree of engagement with the smartphone app and changes in health behaviors and quality of life scores after 12 weeks and 1 year.

**Results:**

A total of 15 patients are randomized as of December 15, 2019 with a mean (SD) age of 66.1 (5.8) years. The majority are female (60%) and black (87%). At baseline, the mean (SD) ABI and 6MWT were 0.86 (0.29) and 363.5 m, respectively. Enrollment is expected to continue until December 2020 to achieve a target size of 50 participants.

**Conclusions:**

The potential significance of this trial will be to provide preliminary evidence of a home‐based, “mobile‐first” approach for delivering a structured exercise rehabilitation program. Smartphone‐enabled HBET can be potentially more accessible than center‐based programs, and if proven effective, may have a potential widespread public health benefit.

## INTRODUCTION

1

An estimated 8.5 million Americans (or 7.2% of the US adult population) are estimated to have peripheral arterial disease (PAD), defined as an ankle‐brachial index (ABI) of <0.9.^1^ Nearly, 10% of PAD patients are symptomatic with claudication—a reproducible leg pain with ambulation that is relieved with rest.^2^ Following the onset of symptoms, patients with PAD are at an increased risk of adverse outcomes including worsening functional status, amputation, myocardial infarction, stroke, and death.^1^, ^3^ African Americans in particular are at an increased risk of PAD and experience greater walking impairment and more severe disease than non‐Hispanic white individuals.^4^, ^5^

Supervised exercise therapy (SET), a 12‐week program with multiple in‐person weekly sessions, is recommended as a first‐line therapy in symptomatic PAD.^6^ Current guidelines for SET include that participants perform intermittent bouts of treadmill‐based walking exercise at least three times per week. During each session, patients are advised to walk in intervals with an intensity level to induce moderate to moderately‐severe leg symptoms within 5 to 10 minutes, at which point they should rest until the pain dissipates. Walking intervals should be repeated with a goal of accumulating up to 60 minutes of total exercise time during each session.^7^ Participation in SET has been shown to improve walking ability, overall functional status, and health‐related quality of life (QoL) in symptomatic PAD, and is considered first‐line therapy with a Class I recommendation from established practice guidelines in patients with claudication.^8^, ^9^

Despite the benefits, SET remains significantly underutilized among eligible patients.^10^, ^11^ In a recent meta‐analysis, less than 25% of patients with claudication enrolled in SET.^10^ Participation in SET has been limited by a lack program availability, poor reimbursement, inconvenience, and patient motivation.^12^ Even despite a National Coverage Determination by the Centers of Medicare and Medicaid Services in 2017 for SET reimbursement, the availability and uptake of SET programs have remained exceedingly low.^13^ This suggests that SET may remain an unlikely option for many patients, especially in low‐resource, public‐hospital settings where third‐party payer coverage for healthcare services is limited.

Home‐based exercise therapy (HBET) has been proposed as an alternative for patients with limited access to facility‐based SET.^6^, ^14^ Structured, home‐based programs have the potential to be a more convenient and acceptable option for patients than supervised exercise.^14^ Although several randomized trials have documented improved walking ability and QoL from HBET over usual care, more recent trials have failed to confirm these findings.^15^, ^16^, ^17^, ^18^, ^19^

### Rationale for the smart step study

1.1

Smartphone ownership is on the rise^20^ and new opportunities exist to efficiently provide services with wider accessibility without increases in personnel and capital resources. Smartphones have been used to successfully deliver home‐based cardiac rehabilitation (CR), a program similar in broad scope and design to HBET for PAD, with high adherence and low attrition.^21^, ^22^ Although several ongoing studies are also evaluating smartphones for various exercise applications in PAD,^23^, ^24^ Smart Step is the first study, to our knowledge, to assess the potential for smartphones to deliver HBET in a low resource, public hospital setting with an economically disadvantaged population. We recently showed the feasibility of smartphone‐enabled CR within the Department of Veterans Affairs with high adherence (90%) and satisfaction (80%) and a 20% gain in functional status.^25^ Based on knowledge gained from this endeavor, we designed the Smart Step Study to help PAD patients overcome similar barriers to SET participation.

### Hypotheses and objectives

1.2

The overarching goal of the Smart Step Study is to evaluate the feasibility of a smartphone‐enabled, home‐based exercise program for PAD in a low‐resource setting where access to a traditional, facility‐based SET program is essentially absent. The primary outcome of interest is functional improvement after 12‐weeks of enrollment. We will also assess for participant engagement with the smartphone app and phone‐based coaching. If successful, this study will generate novel information on how PAD patients in economically disadvantaged settings respond to a smartphone‐based exercise program and provide evidence to proceed with larger trials to determine efficacy.

## METHODS

2

### Trial design and oversight

2.1

The Smart Step Study (ClinicalTrials.gov NCT03479255) is a single‐site, prospective, open‐label, pilot randomized trial of patients with symptomatic PAD who are eligible for SET. The study design is illustrated in Figure 1. Eligible subjects are randomized to either a smartphone‐enabled HBET program or to walking advice with standard exercise guidance. Potential participants are recruited from the vascular surgery and cardiology clinics at Grady Memorial Hospital, a tertiary academic medical center and public benefit hospital in downtown Atlanta, GA, and screened for eligibility. Eligible participants are then randomized in a 1:1 ratio using a random number generator. Women are oversampled to achieve a 50% target representation. The study protocol has been approved by the Institutional Review Board at Emory University and the Research Oversight Committee at Grady Memorial Hospital.

**FIGURE 1 clc23362-fig-0001:**
[figure not shown]
Smart step study design. Data as of December 2019

The study was designed by the Executive Committee which includes three cardiologists and three vascular surgeons. Funding was provided by the Emory Woodruff Health Sciences Center. The industry partners (Moving Analytics and INTERVENT) were not involved in the study design and did not provide funding but are participating in data collection. The Clinical Endpoint and Data Monitoring Committees are located at Emory University.

### Eligibility criteria

2.2

Subjects aged 18 to 89 years with evidence of PAD based on a resting ABI ≤0.90 and clinically stable intermittent claudication as determined by the referring physician are eligible. All participants must have a personal Android (Google, Mountain View, California) or iOS (Apple, Cupertino, California) smartphone in working condition and be able to provide informed consent. Those with both typical and atypical symptoms of claudication are also considered, as prior studies have demonstrated that patients with atypical symptoms also have significant functional limitation that improves significantly with supervised exercise.^26^, ^27^, ^28^, ^29^ Patients are excluded if they have any life‐threatening conditions (eg, sepsis, unstable angina, or New York Heart Association [NYHA] class IV heart failure), critical limb ischemia, or a condition other than PAD that causes limitation in walking before the onset of claudication. Detailed inclusion and exclusion criteria with justifications are listed in Table 1.

**TABLE 1 clc23362-tbl-0001:** Inclusion and exclusion criteria

Inclusion criteria
Age 18‐89 years Able to provide informed consent Clinically stable intermittent claudication Diagnosis of peripheral arterial disease (PAD) with one of the following: Ankle‐brachial index (ABI) ≤ 0.9 or ABI > 0.9 but ≤1.00 at rest with 20% drop in ABI with exercise or heel‐rise test or ABI > 0.9 with other evidence of lower extremity PAD such as a positive anatomic study (ie, ultrasound, computed tomography or invasive angiography) or prior lower extremity revascularization (surgical or endovascular) for PAD or ABI > 1.3 with additional evidence of PAD (ie, pulse volume recording [PVR], toe‐brachial index or arterial duplex studies). Possess a working Android or iOS smartphone to install the Movn app

Exclusion criteria	Justification
1. Individuals whose walking is limited by a condition other than PAD (eg, severe angina or dyspnea, arthritis, muscle weakness or pain).	Intervention is designed to improve PAD related walking impairment.
2. Any life‐threatening process including (eg, sepsis, critical limb ischemia [Rutherford class 4‐6], unstable angina, active malignancy with life expectancy <6 months, severe New York Heart Association [NYHA] Class IV heart failure)	Exercise may be potentially unsafe for these patients.
3. Active behavioral conditions such as uncontrolled schizophrenia or illicit drug addiction that, in the opinion of the study team, will interfere with active participation.	May interfere with ability to fully engage in the study.

### Study procedures and follow‐up

2.3

Upon enrollment, participants are randomly assigned to either the smartphone‐enabled HBET or usual care arm and followed prospectively for 12 weeks. Regardless of the treatment arm, all subjects receive a Fitbit Charge 2 (Fitbit, San Francisco, California) to record various measures of physical activity including steps, exercise activity, and heart rate (HR). All participants are then prescribed an exercise plan according to their study arm as outlined below.

#### Standard exercise therapy

2.3.1

Patients randomized to the usual care arm receive counseling by their physician to perform self‐monitored walking exercise according to established practice guidelines for PAD. This represents current standard practice at Grady Memorial Hospital and includes a recommendation to perform between 30‐ and 45‐minutes walking exercise three times per week. This is based on prior meta‐analyses which have found that walking at least 30 minutes is more beneficial than shorter durations, and that benefit appears to peak at 45 minutes.^9^, ^30^, ^31^ Participants are instructed to walk at an intensity that induces onset of claudication within 3 to 5 minutes and moderate to moderately severe claudication within 8 to 10 minutes, at which point they should stop and rest until their claudication subsides. After their symptoms dissipate, they should resume this same cycle of exercise until their target exercise duration is reached. In addition to exercise, participants in the standard exercise group receive counseling on healthy lifestyle behaviors including dietary changes, medication adherence, and smoking cessation if needed.

#### Smartphone‐enabled exercise therapy

2.3.2

Patients in the smartphone‐enabled arm receive an app (Movn, Moving Analytics, Los Angeles, California) to guide their exercise program in addition to the fitness tracker which also synchronizes with the app. Our study team has successfully piloted the use of Movn in the delivery of home‐based CR to veterans with ischemic heart disease.^25^ Movn is a commercially available home‐based exercise rehabilitation program based on the MULTIFIT,^32^ a case‐management system for secondary prevention and patient surveillance after acute MI developed by investigators at Stanford University School of Medicine and implemented within Kaiser Permanente of Northern California. In previous studies, MULTIFIT has been shown to significantly improve low‐density lipoprotein cholesterol (LDL‐C) levels, functional capacity, and rates of smoking cessation after 12 weeks of enrollment compared to usual care.^32^, ^33^ Movn provides virtual delivery of MULTIFIT through a patient‐facing smartphone app that synchronizes with a provider‐facing online case‐management dashboard to allow for remote monitoring of participants' progress (Figure 2). The app includes a virtual diary for participants to enter data on exercise sessions (including exercise time, frequency and symptoms), blood pressure (BP), HR, weight and medication adherence, as well as provide exercise reminder notifications, educational material on heart and vascular health, and two‐way secure messaging with a health coach. The coach is an exercise physiologist with extensive experience in remote coaching (via INTERVENT, Savannah, Georgia). The initial coaching session occurs via video conference and subsequent sessions are performed with brief telephone calls lasting approximately 15 minutes in duration. Customized education modules designed by INTERVENT are used to specifically educate the participants on PAD. The coach facilitates each participant's exercise program by remotely monitoring their progress via the dashboard and providing feedback during scheduled telephone calls occurring at 1 to 2‐week intervals. Participants in the smartphone‐enabled arm receive the same educational topics and guideline‐directed exercise prescription as for the standard exercise arm.

**FIGURE 2 clc23362-fig-0002:**
[figure not shown]
Movn smartphone app and dashboard

### Study measures

2.4

The primary outcome changes in 6‐minute walk distance between baseline and 12 weeks. Secondary outcomes include (a) changes in disease burden and health‐related QoL scores at 12 weeks and 1 year (b) changes in daily ambulatory activity measured by the Fitbit, and (c) degree of engagement with the app and coaching program. A full list of study measures along with timing of measurements are included in Table 2. There are no exploratory endpoints. All prespecified outcomes are obtained by trained study staff. Based on the nature of the intervention requiring logistical coordination with Moving Analytics and INTERVENT for treatment allocated patients, blinding was not considered feasible.

**TABLE 2 clc23362-tbl-0002:** Study measures

	Time point		
	Baseline	12 weeks	1 year
Primary endpoint			
6‐minute walk test distance	X	X	X
Secondary endpoints			
Walking Impairment Questionnaire	X	X	X
Short Form‐36 questionnaire	X	X	X
Smartphone app and Fitbit usage	X	X	X
Ambulatory activity (average daily steps)		X	X
Peripheral artery disease risk factors	X	X	X
Clinical endpoints (all‐cause emergency department and hospital admissions, critical limb ischemia, cardiovascular events including acute coronary syndromes and stenting, and all‐cause mortality)		X	X

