#### Key endpoints

2.5.1

Our primary outcome is change in 6MWT distance from baseline to 12 weeks (ie, end of program completion). All remaining outcomes are secondary and include survey data from the WIQ and SF‐36 questionnaires, changes in daily ambulatory activity from the Fitbit, modifiable PAD risk factors (such as blood pressure and smoking status), self‐reported exercise and medication adherence collected via the smartphone app, the degree of participant engagement with the app individual features (eg, chats, educational videos), and pre‐specified clinical endpoints (eg, emergency department visits, hospital admissions, critical limb ischemia, cardiovascular events, or death prior to program completion).

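### A secondary endpoint is the change in Fitbit daily activity, but the schedule has no baseline step measurement and the procedures describe no wear period before the intervention

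*Protocol article*

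**What the plan says.** Section 2.4 (Study measures) names "changes in daily ambulatory activity measured by the Fitbit" as secondary outcome (b). Section 2.5.1 (Key endpoints) repeats it as "changes in daily ambulatory activity from the Fitbit".

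Section 2.4 then points to the schedule: "A full list of study measures along with timing of measurements are included in Table 2". In that table the row beginning "Ambulatory activity (average daily steps" is marked at 12 weeks and 1 year, and its baseline cell is empty. The row "Smartphone app and Fitbit usage" is marked at all three time points.

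Section 2.3 (Study procedures and follow-up) opens with "Upon enrollment, participants are randomly assigned to either" arm, continues with "Regardless of the treatment arm, all subjects receive a Fitbit Charge 2", and then says that each participant is given the exercise plan for the assigned arm. Section 2.4.3 describes daily wear and minute-level step recording but names no reference period.

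**The concern.** A change endpoint needs a starting value. The text promises a change and the schedule provides no starting value, so the analyst must either drop the word or find a substitute. The obvious substitute is early Fitbit wear, because the device records continuously. As section 2.3 reads, that wear falls after the program has been prescribed. In the smartphone arm it may already contain part of what the app and the coach achieve, and subtracting it would then remove real effect.

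A second risk is that day 1, week 1 and week 2 are all possible stand-ins and the article fixes none of them. In an open-label trial that choice should not be made after the step data have been seen.

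Daily steps are also the only device-measured outcome of everyday activity in both arms. The WIQ and SF-36 are completed by participants who know their allocation, so the step endpoint is a useful complement and deserves a clean definition.

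**Working it through.** **Endpoint against schedule**

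| Table 2 row | Baseline | 12 weeks | 1 year |
|---|---|---|---|
| 6MWT distance | X | X | X |
| WIQ | X | X | X |
| SF-36 | X | X | X |
| PAD risk factors | X | X | X |
| App and Fitbit usage | X | X | X |
| Average daily steps | – | X | X |
| Clinical endpoints | – | X | X |

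The empty cell does not look like a fault of text extraction. The clinical-endpoints row has the same pattern, where an empty baseline makes sense, and the other rows show three marks. The usage row does not supply a baseline for steps, because it records use of the app and device and steps have their own row. The only change that can be formed from the scheduled step values is 12 weeks to 1 year, which is not a change over the 12-week program.

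**Effect of a stand-in baseline**

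Notation: μ is the untreated mean daily step count; c is any early effect common to both arms (new device, general exercise advice); e is the common effect at the end of the program; Δ is the true between-arm difference at the end; f is the share of Δ already present in the early window.

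- Smartphone arm: early mean μ + c + fΔ; end mean μ + e + Δ.
- Usual care arm: early mean μ + c; end mean μ + e.
- Difference in changes: (e + Δ − c − fΔ) − (e − c) = (1 − f)Δ.
- Difference in end levels: (μ + e + Δ) − (μ + e) = Δ.

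The common terms cancel, so the loss comes only from early app and coach effects. The documents give no value for f. Over an assumed range, f = 0 leaves Δ, f = 0.25 leaves 0.75Δ, and f = 0.5 leaves 0.5Δ. The comparison of end levels is unbiased because randomisation makes μ equal in expectation.

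**Precision without a baseline**

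The plan gives no power figure for steps. Its own figure for the 6MWT, a minimum detectable difference of 45 m with SD 57 m and 25 per arm, serves to check the method: (1.960 + 0.842) × √(2/25) = 0.793 SD, and 0.793 × 57 = 45.2 m, which agrees. The t-distribution version is 0.81 SD (46.1 m) and is used below.

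Let r be the correlation between baseline and follow-up steps (an assumption; it is not in the documents). Detectable differences with 25 per arm, 80% power and two-sided 5%, in SD units:

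| Analysis | Formula | r = 0.3 | r = 0.5 | r = 0.7 | r = 0.8 |
|---|---|---|---|---|---|
| End level only | 0.81 | 0.81 | 0.81 | 0.81 | 0.81 |
| Change from a true baseline | 0.81 × √(2(1 − r)) | 0.96 | 0.81 | 0.63 | 0.51 |
| Adjusted for a true baseline | 0.81 × √(1 − r²) | 0.77 | 0.70 | 0.58 | 0.49 |

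The third formula also applies to adjustment for baseline 6MWT distance, with r read as the correlation of that distance with follow-up steps: 0.77 SD at 0.3 and 0.70 SD at 0.5.

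**The case against.** The strongest reply is that the endpoint can still be computed. The Fitbit records continuously, so a change from the first days of wear is available for anyone who wears it, and so is a change from 12 weeks to 1 year. Step levels at 12 weeks can be compared between arms with no baseline at all. This stands. A reader might infer that the endpoint cannot be computed, or is undefined for all 50 participants; the documents do not support that. What is unavailable is a change from a pre-intervention value.

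A reader might also take it as stated fact that the device is issued only after randomisation. Section 2.3 gives that order in its sentences but never says so outright, and the design figure is not shown. The conflict between the endpoint wording and Table 2 does not depend on this point.

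It is tempting to conclude that the usage and step rows had their baseline marks exchanged in error. Nothing in the document confirms this. If it were so, a baseline step measurement was planned and the defect would be typographical.

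Nor is early wear contaminated by everything participants receive. Both arms get the Fitbit and the same guideline-directed exercise prescription, so those effects largely drop out of the contrast, as the algebra shows.

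Finally, a condensed article may leave the step-averaging window to a fuller document. That is fair, and the missing window alone is no finding. The finding is that the article states an endpoint and a schedule it calls full, and the two disagree.

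**Conclusion.** The point holds as an inconsistency between a named secondary endpoint and its measurement schedule. Under the schedule and procedures as written, a change in steps from a pre-intervention baseline is not available. An early-wear substitute would estimate (1 − f)Δ instead of Δ, with f unknown.

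The conclusion takes Table 2 as complete, as the article says it is. The view that early wear falls under the assigned program also rests on the order of sentences in section 2.3. The values of f and r shown are assumptions for scale, not estimates.

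Severity is moderate. This is one of several secondary endpoints in a pilot powered on the 6MWT alone. The 6MWT has its baseline measurement, so the primary analysis and the sample size are unaffected.

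**What to change.** In sections 2.4 and 2.5.1, replace the change wording with mean daily steps over a fixed window at the end of the 12-week program (for example its last two weeks), and correspondingly at 1 year. Compare the arms, adjust for baseline 6MWT distance, and state that early-wear steps are not subtracted. Leave the Table 2 baseline cell for steps blank, which then matches the definition.

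If a wear period before randomisation was in fact used, describe it in section 2.3, mark it in Table 2, and use those steps as a covariate instead.

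The redefinition costs only wording and applies to every participant, including the 15 already randomised. It should be settled before between-arm step data are examined. The statistical price is the precision that a true baseline would have given: 0.81 SD detectable before any gain from 6MWT adjustment, against 0.70 to 0.49 SD with baseline-step adjustment at assumed correlations of 0.5 to 0.8.
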